#### 2.1.9. Statistical Analysis

A sensitivity of 95% and specificity of 90% is sufficiently accurate to be incorporated into clinical practice. If confirmed, they will make supermarkets with in-store pharmacies a nationwide relevant and cost-effective point of screening AF. Such high sensitivity and specificity values are also indicated as plausible by existing published papers, with 95% confidence intervals of 93–100% and 91.3–98.1% [29] and 87–98% and 85–97% [28], for sensitivity and specificity, respectively. In our proposed feasibility study, our precision calculations show that with between 21 and 76 AF cases, we will estimate the 95% confidence interval of sensitivity and specificity with interval widths of 19.0% and 9.8%. The most likely precision will be 12.4%.

Descriptive statistics including simple percentages will be estimated from this feasibility study to demonstrate uptake, rates of detection and successful referral. Generating these data will enable the researchers to determine the number of shoppers who need to be approached to recruit for an adequately powered future study. In addition, conditional percentages will be used to describe the sensitivity and specificity of both the sensor and the pulse check.

By recruiting from community supermarkets based in areas of high deprivation, it is likely that we will recruit a greater number of individuals who are known not to typically engage in traditional screening programmes. This approach attempts to correct the inverse care law, bringing healthcare to the community.

### 2.2. Phase 2

The second phase of the study involves an embedded qualitative approach. The primary objective is to explore the views of supermarket-based pharmacists and store managers on the merits of embedding pulse sensors in the handles of supermarket trolleys to enable the detection of AF. The secondary objective is to explore the pharmacists’ perspectives and experiences of performing manual pulse checks on participants.

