#### 2.1.3. Sample Size

Large supermarkets attract an average footfall of 25,000 people per week [23], providing a potential total population across four stores per week of 100,000 people. Recognising that many of these people are returning customers attending on a weekly basis, this study aims to recruit around 2% of the total population, resulting in a sample of 2000 participants. The prevalence of AF in the area of the North West of England from which participants are to be recruited is estimated to be 2.1% [24,25], which would result in 42/2000 positive results, including some who are known to experience AF. However, we recognise that those most at risk of developing AF are ≥ 65 years. Unfortunately, neither the British Retail Consortium nor YouGov provides age-related data for in-store supermarket shopping. One American study estimated that those over the age of 60 years make up 24% of supermarket consumers [26]. Recognising that the prevalence of AF is highest in this older age group, ranging from 4–11% in those 65–79 years old, we estimate a total of 480/2000 people will be screened from within this age group and between 19/480 and 53/480 people will be found to be in AF. In addition, it is estimated that the remaining 1520 customers present between 0.1–1.5% risk of AF suggesting between 2/1520 and 23/1520 additional presentations. In total, it is estimated that between 21 and 76 participants will be found to be suffering AF [27]. The prevalence of undiagnosed AF differs dependent on age. A systematic review of 30 single time-point AF screening studies including 122,571 participants (Lowres et al., 2013) reported the incidence of previously unknown AF as 1.0% (CI, 0.89–1.04%), increasing to 1.4% (CI, 1.2–1.6%) in those >65 years old. We recognise that we are recruiting a yonger population than those included in these studies, we therefore estimate that up to 28 people will be identified with undiagnosed AF.

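### The stated confidence-interval widths are normal-approximation widths for sensitivity only: they do not apply to specificity, are too narrow for sensitivity at 21 to 76 cases, and the 12.4% fits 47 to 48 cases rather than 42

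*Protocol article*

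**What the plan says.** Section 2.1.9 takes as its benchmark that "A sensitivity of 95% and specificity of 90% is sufficiently accurate to be incorporated into clinical practice". Its precision figures rest on the range of AF cases carried over from section 2.1.3, and one pair of widths is given for both measures: "we will estimate the 95% confidence interval of sensitivity and specificity with interval widths of 19.0% and 9.8" per cent. A single central figure is then added: "The most likely precision will be 12.4" per cent. The section names no interval method and gives no case number for the 12.4%.

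The case numbers come from section 2.1.3, which has two routes. A local prevalence of 2.1% gives a single expectation, "which would result in 42/2000 positive results, including some who are known to experience AF". An age-stratified estimate gives a range: "In total, it is estimated that between 21 and 76 participants will be found to be suffering AF". The total of 2,000 is derived from store footfall: "this study aims to recruit around 2% of the total population, resulting in a sample of 2000 participants".

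**The concern.** Sensitivity is a proportion among people with AF, and specificity a proportion among people without it. The sentence ties both to the number of AF cases and gives them one pair of widths. In a sample of 2,000 with at most 76 cases, the two denominators differ by a factor of at least 25 (1,924/76).

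Two further features prompted a check. A 95% proportion in as few as 21 people is a setting where the usual normal-approximation interval behaves badly. And the most likely figure would naturally be expected to rest on the 42 cases that section 2.1.3 derives from prevalence.

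At stake is what a reader takes from the only precision statement in the article: sensitivity would look better determined, and specificity much worse determined, than the planned numbers imply.

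**Working it through.** **Inputs.** Sensitivity 0.95 and specificity 0.90 (section 2.1.9); AF cases 21 to 76, with 42 at 2.1% prevalence, and total 2,000 (section 2.1.3). People without AF, by subtraction: 2,000 − 76 = 1,924; 2,000 − 42 = 1,958; 2,000 − 21 = 1,979.

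**1. Reproducing the stated widths.** The full normal-approximation (Wald) width is 2 × 1.96 × √(p(1−p)/n). With p = 0.95:

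- n = 76: 2 × 1.96 × √(0.0475/76) = 9.80%. The article states 9.8%.
- n = 21: 2 × 1.96 × √(0.0475/21) = 18.6%. The article states 19.0%; n = 20 gives 19.1%.

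The end points are therefore Wald widths for sensitivity, exactly at 76 cases and within 0.4 points at 21.

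**2. The 12.4%.** At n = 42 the same formula gives 13.2%. Solving for n gives 4 × 1.96² × 0.0475/0.124² = 47.5 cases (47 cases give 12.5%, 48 give 12.3%). The midpoint of 21 and 76 is 48.5, which gives 12.3%. So 12.4% sits near the midpoint of the range and not at 42.

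**3. Specificity.** With p = 0.90 on the non-AF denominator:

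- n = 1,924: 2 × 1.96 × √(0.09/1,924) = 2.68%
- n = 1,958: 2.66%
- n = 1,979: 2.64%

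Exact (Clopper-Pearson) widths are 2.7% throughout. If the pair means sensitivity 19.0% and specificity 9.8%, the specificity figure is 9.8/2.66 = 3.7 times too wide. If the pair is a range for both measures, its upper end is 19.0/2.66 = 7.1 times too wide. Conversely, at 90% a width of 9.8% corresponds to 4 × 1.96² × 0.09/0.098² = 144 people without AF, and 19.0% to 38. Neither number follows from the article.

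**4. Whether the Wald width suits sensitivity here.** Full widths at p = 0.95, in percentage points, taking 0.95n as the number detected:

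| AF cases | Stated | Wald | Wilson | Exact |
|---|---|---|---|---|
| 21 | 19.0 | 18.6 | 22.1 | 24.0 |
| 42 | – | 13.2 | 14.7 | 15.8 |
| 76 | 9.8 | 9.8 | 10.5 | 11.3 |

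At 21 cases the Wald upper limit is 95 + 18.6/2 = 104%, which is impossible. All 21 cases would be detected with probability 0.95^21 = 34%, and the Wald interval then has zero width. Summing binomial probabilities at a true 95%, Wald coverage is 66%, 88% and 89% at 21, 42 and 76 cases.

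**The case against.** The best defence is that the figures are mostly right for what they evidently are. A reader might infer that the whole statement fails to reproduce. It does not: 9.8% is exact and 19.0% nearly so, as Wald widths for sensitivity.

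Nor does section 2.1.9 tie 12.4% to 42 cases. The figure follows directly on the range 21 to 76 and suits its midpoint, and the gap to 13.2% is 0.8 points. What stands is that the case number is unstated and differs from the only single expectation in section 2.1.3.

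It can also be said that narrowness is a matter of method rather than arithmetic, and that the exact interval is the conservative extreme. That is fair: at 21 cases a Jeffreys interval is 20.0 points wide. The article does not commit to reporting Wald intervals, so the coverage of 66% is a reason against planning on that formula. It is not a forecast of what the study will report. Still, Wilson, a milder choice than exact, exceeds the stated widths at both ends of the range.

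Two stronger readings are tempting and unsupported. One is that the sample size rests on these widths and falls with them; section 2.1.3 derives 2,000 from footfall. The other is that the definitive trial would be planned from wrong error bars; section 2.1.9 says it will use the uptake, detection and referral percentages that the study observes.

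No part of this defence rescues the specificity widths. It does show that the error there makes the study look less precise than its nominal numbers allow.

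**Conclusion.** The point holds in three parts of unequal weight.

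- **Specificity:** the stated width is wrong on either reading, by a factor of about 3.7, or about 7 if 19.0% is also meant for specificity. The error is conservative.
- **Sensitivity:** the stated widths are optimistic for these counts. Against 19.0 and 9.8, Wilson gives 22.1 and 10.5 points, and exact gives 24.0 and 11.3.
- **Most likely figure:** 12.4% fits 47 to 48 cases. At 42 it is 13.2% by the same formula, 14.7% by Wilson and 15.8% exact.

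These results assume true values of 95% and 90% and the article's own case numbers. The 2.7 points for specificity further assumes a usable reference result in every participant without AF. That is not secure: section 2.1.8 describes 12-lead ECGs for those referred, and section 2.1.7 gives sensor-negative participants a manual pulse check. The article does not say how many would count. As an illustration only, 1,000 usable non-AF results would give 2 × 1.96 × √(0.09/1,000) = 3.7 points, and 500 would give 5.3.

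No decision rule and no sample size depends on these numbers, so this is a should-fix point and not a fatal one.

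**What to change.** Rewrite the precision statement in section 2.1.9 as follows.

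1. Give sensitivity widths at 21, 42 and 76 cases and name the method: about 22, 15 and 10.5 points by Wilson, or about 24, 16 and 11 by exact intervals.
2. State the case number behind the most likely figure, or recompute it at 42.
3. Give specificity separately, on the non-AF denominator: about 2.7 points at 90% if all of roughly 1,958 non-AF participants have a usable reference result. Add that 12-lead ECGs are planned only for those referred, so the number that counts may be smaller and the interval wider.
4. Use the same Wilson or exact method when accuracy is reported.

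The change is to wording only. Sample size, design and conduct stay as they are. The price is a less favourable stated precision for sensitivity.

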#### 2.2.1. Informed Consent

The Senior Store Manager will identify all those staffs who are eligible for the study and will distribute a Participant Information Sheet and Consent Form accordingly. A member of the research team will be available to explain the study to potential participants at a mutually convenient time. All eligible participants will receive information about the study outlining the purpose, potential risks and implications of participation. They will be asked to sign and date an informed consent form that adheres to the ethical principles that have their origin in the Declaration of Helsinki prior to enrolment. The participant information sheet and informed consent form will acknowledge that the study data will be used in academic publications. However, participants will be informed that no personal or identifiable data will be shared outside the research team. All data will be anonymised prior to publication.

#### 2.2.2. Study Design

Qualitative interviews will be undertaken to explore the views of pharmacists and store managers. All pharmacists and store managers from each supermarket will be invited to participate in a qualitative interview. Store managers are defined as any manager with responsibility for managing the store during the study period. Pharmacists are defined as being General Pharmaceutical Council (GPhC) registered and employed in the store. All participants must be able to provide written informed consent and devote time to attend the interview. The exclusion criteria include previous participation in the study in the event of a store manager or pharmacist transferring to a neighbouring store during the study period and absence from the store during the entirety of the data collection period.

#### 2.2.3. Recruitment

A convenience sample including store managers and GPhC registered pharmacists employed within the supermarket within the study period will be recruited. Each store manager will identify potential participants.

#### 2.2.4. Study Procedures

We will undertake individual semi-structured interviews with all store managers and pharmacists that have engaged in the screening study. The interviews will focus on exploring the supermarket employees’ views on the merits of embedding sensors in the handles of the supermarket trolleys, the impact of using these trolleys to screen for AF on the workload of the pharmacists and the efficiency of the stores and identify any additional customer feedback that may have been received. The procedure for Phase 2 is outlined in Figure 5.

#### 2.2.5. Data Analysis

Thematic analysis using the qualitative data generated from the interviews with pharmacists and store managers will be independently analysed by two members of the research team adopting Braun and Clarke’s (1996) framework for thematic analysis [32].

#### 2.2.6. Patient and Public Involvement (PPI)

The Service Users for Research Endeavour (SURE) group at Liverpool Heart and Chest Hospital and the patient and public involvement group at the Liverpool Centre for Cardiovascular Science will review the research protocol, participant information sheet and consent form. Their advice will be sought throughout the design of the study.

#### 2.2.7. Ethical Considerations

The ethical review has been granted by Liverpool John Moores University’s University Research Ethics Committee. The study will be undertaken in compliance with the research protocol. During Phase 1, verbal consent will be obtained upon recruitment, with written consent secured for those with an abnormal sensor recording whose personal data will be required for onward referral for 12 lead ECGs. For the qualitative sub-study (Phase 2), written consent will be obtained for all participants.

## 3. Discussion

Many people with AF are undiagnosed, unaware and are subsequently at increased risk of stroke and mortality compared with people with symptomatic AF [33,34,35]. The reasons for these differences are unclear but are likely to occur because of limited preventative treatment, such as anti-coagulation and inadequate management of additional risk factors.

The high economic and individual burden of AF makes early identification through screening an attractive proposition to clinicians, patients and budget holders alike. However, trial data to support AF screening models are scarce [36,37]. Opportunistic screening has been found to be cost-effective [38] but remains reliant on a substantial health resource. Consequently, there is increasing interest in the use of patient-initiated ECG or photoplethysmography screening, with >100 mHealth apps and ≥400 wearable activity monitors reportedly available [39]. However, patient-initiated screening can be expensive to the consumer and consequently excludes those with lower household incomes. Moreover, this form of screening is dependent on individuals with few or no symptoms actively purchasing and participating in a screening ritual. Furthermore, the number of e-health applications is increasing exponentially with little or no scrutiny of their efficacy. It is therefore inevitable that the public will be exposed to poor-quality devices with limited accuracy, the results of which will lead to a combination of false reassurance for some and an inappropriate use of healthcare resources for others. Introducing sensor-based screening into everyday activities with immediate access to resident health care professionals could provide a means of capitalising on the improvements in technology whilst negating the need for individuals to invest in said technology and, in doing so, revolutionise the way that healthcare screening is offered.

This proposed study aims to introduce the concept of using sensor-based diagnostic technology in everyday activities whilst ensuring that all participants have access to a defined healthcare pathway, thus optimising the benefits that early diagnosis provides. The study design will allow the researchers to assess the acceptability of the concept, the efficacy of the sensors and the engagement of those found to be in AF. Finally, the study will address the uncertainties in optimal trial design to inform a future definitive trial.

## Figures and Tables

**Figure 1 jpm-12-00578-f001:**
[figure not shown]
MyDiagnostick single lead ECG sensor embedded into the handles of supermarket trolleys to detect atrial fibrillation. A participant should place both hands around the device for 60 s. Depending on the detection of atrial fibrillation or not, the sensor will present with a red cross or a green tick, respectively.

**Figure 2 jpm-12-00578-f002:**
[figure not shown]
A single lead ECG tracing showing AF.

**Figure 3 jpm-12-00578-f003:**
[figure not shown]
A single lead ECG tracing that was recorded as not AF.

**Figure 4 jpm-12-00578-f004:**
[figure not shown]
Phase 1 (Quantitative) procedure to follow regarding those participants to be recruited in a cross-sectional observational study determining the effectiveness of sensor technology to detect atrial fibrillation (AF) when embedded in the handles of supermarket trolleys. A minimum of two thousand participants will be recruited. A convenience sample will be used.

**Figure 5 jpm-12-00578-f005:**
[figure not shown]
Phase 2 (Qualitative) procedure to follow when conducting semi-structured interviews exploring the views of supermarket-based pharmacists and store managers around the use of sensor technology to detect atrial fibrillation (AF) when embedded in the handles of supermarket trolleys.
